### Data collection and management

2.7

The study will be conducted with two-time measurement periods, each 6 weeks long, whereby caregivers will complete an online questionnaire via online survey based on the CCQ and the NCI-CTCAE Scales describing gastroenterological-based symptoms at the end of each week of the data collection period.

At the beginning of each measurement period, caregivers will be asked to complete an initial onboarding questionnaire containing socioeconomic background information about the family. The first measurement period will be planned in autumn 2022, followed by a second measurement in the autumn of 2023 (see Figure 3: Data Collection Flowchart).

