The onboarding and weekly questionnaires will be sent using the collected parent emails using the Charité version of the software SoSci (Program-Version 3.5.00).

After an initial invitation, caregivers who have not completed the survey will be reminded to complete it on a weekly basis over 6 weeks. Additionally, a study assistant (AT) will contact caregivers of missing entries via telephone. In addition to the online entries, the missed kindergarten days will be documented by the kindergarten facilities and likewise measured at the two time points for 6 weeks at baseline and 12 months after baseline.

The total number of kindergarten educator sick days will also be documented without descriptive personal data and kindergartens will report the used interventions weekly to the study assistant.

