### Statistical methods

2.8

The study will be published in a peer-reviewed academic journal. Analyses of data will be performed after the collection is finalized according to the following hypotheses:

Primary Efficacy Hypothesis (Infection days leading to absence):Primary Null Hypothesis (H0): Implementation of a child-friendly Kneipp concept in the kindergartens does not lead to a significant reduction in infection-related absenteeism, after 12 months.Alternative Hypothesis (H1): Implementation of child-friendly Kneipp concept in the kindergartens results in a significant reduction in infection-related absenteeism, after 12 months.

Participant characteristics, stratified by groups (Kneipp vs. Control) will be presented. For continuous variables, descriptive statistics such as mean, standard deviation, and range will be calculated, while frequencies and percentages will be used for categorical variables.

The primary outcome will be the number of sick days reported to the kindergarten. To account for the expected overdispersion (right-skewed data because of high zero counts) in the count data, we will employ a negative binomial regression model. This model will include the group (Kneipp vs. Control) and the number of sick days at baseline as predictors. We will integrate unique kindergarten identifiers to determine if cluster effects exist.

For secondary outcome analysis, we will conduct an independent t-tests to compare the mean Common Cold Questionnaire (CCQ) scores between the Kneipp and Control groups. To investigate the interaction effects of group and sex, and group and age on CCQ scores, a two-way ANOVA will be performed. This model will include the main effects of group, sex, and age, as well as their interactions. If significant interactions are identified, post-hoc analyses will be conducted. Correlation analysis will involve calculating Spearman’s correlation coefficients to assess the relationships between CCQ scores and the number of sick days, and between CCQ scores and age. The correlation (ρ) will be interpreted based on conventional guidelines. To compare the frequencies of health outcomes such as colds, bronchitis, lung inflammation, antibiotic use, and gastrointestinal infections between the Kneipp and Control groups, chi-square tests will be performed. If the assumptions of the chi-square test are violated due to expected frequencies being less than 5, Fisher’s exact test will be used instead.

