The compliance analysis will be conducted by considering both the Intention-to-Treat (ITT) and Per-Protocol (PP) populations. The ITT population will include all children from whom kindergarten reports are available. The PP population will consist of children who strictly followed the prescribed treatment and for whom complete data is available.

For handling missing data in the ITT approach, multiple imputation will be used. Sensitivity analyses will also be performed to compare the results from the ITT and PP approaches to ensure robustness of the findings.

To ensure the validity of our model assumptions, normality of the data distribution for continuous outcomes will be assessed using the Shapiro–Wilk test. If necessary, data will be transformed using appropriate methods, such as log transformation, to meet the assumptions on the statistical tests. All analysis will be considered significant if *p* < 0.05 and will be conducted using R in its current version.

Qualitative data, focused ethnography observation protocols and interview transcripts, will be analyzed with content analysis with a combined deductive and inductive analysis (18).

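### Cold and gastrointestinal symptoms are collected weekly in two six-week windows, but the named chi-square/Fisher test cannot use repeated weeks, weeks answered or the baseline window

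*Protocol article*

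**What the plan says.** Section 2.7 (Data collection and management) of the protocol article sets the design: "The study will be conducted with two-time measurement periods, each 6 weeks long". Caregivers complete an online form based on the Common Cold Questionnaire (CCQ) and the NCI-CTCAE scales for "gastroenterological-based symptoms at the end of each week of the data collection period". A child can therefore supply up to six records in the baseline window and six in the 12-month window. The same section provides weekly reminders and telephone follow-up of missing entries, so incomplete weekly response is expected.

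Section 2.8 (Statistical methods) gives the test for colds, bronchitis, lung inflammation, antibiotic use and "gastrointestinal infections between the Kneipp and Control groups, chi-square tests will be performed". The only exception is for sparse tables: "due to expected frequencies being less than 5, Fisher’s exact test will be used instead". The section does not say whether a frequency counts children, weeks or episodes, or which window is tested. Kindergarten is mentioned only with the primary negative binomial model: "We will integrate unique kindergarten identifiers to determine if cluster effects exist". That model also adjusts for baseline; the chi-square tests do not. Multiple imputation is named for the intention-to-treat approach, without saying to which variables or at what level.

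**The concern.** Chi-square and Fisher tests need one independent observation per unit. Six weekly reports on one child are not independent, and the Fisher fallback deals with small expected counts, not with dependence. To use the named test, the weekly records must first be reduced to a table, and the result depends on how that is done:

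- Counting child-weeks as if each were a separate child understates the variance.
- Counting each child once as ever/never affected keeps the units right at child level. It discards the number of affected weeks, and the chance of being recorded as affected rises with the number of weeks the caregiver answered.

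Neither use draws on the baseline window, although the same data are collected there. These are secondary outcomes, so the confirmatory conclusion on sick days is not at risk. At stake is whether the illness-specific comparisons, which would help explain any effect on absence, can be trusted and are reasonably sensitive.

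**Working it through.** **Inputs from the article (section 2.5 unless stated).** φ = 0.205, two-sided α = 0.05, power 80%, dropout about 20%, 240 children; kindergartens randomised within matched pairs (section 2.6), taken as equal arms; W = 6 weeks per window (section 2.7).

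**Assumptions (not in the article).** Within-child correlation of weekly reports ρ = 0.1-0.3; weekly prevalence p = 5%, 10% or 30%; true weekly ratio 0.7 for power; no kindergarten effect unless stated.

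**Step 1. The plan's own figure.** N = (1.960 + 0.842)² / 0.205² = 186.8, so 187; 187 / 0.8 = 233.75, so 234, within 3% of 240. The figure reproduces. After 20% dropout, 240 × 0.8 = 192, or 96 per arm, which is used below.

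**Step 2. Child-weeks pooled as independent.** Design effect DE = 1 + (W − 1)ρ; actual two-sided α = 2[1 − Φ(1.96/√DE)].

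| ρ | DE | actual α |
|---|---|---|
| 0.1 | 1.5 | 0.110 |
| 0.2 | 2.0 | 0.166 |
| 0.3 | 2.5 | 0.215 |

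Beta-binomial simulation (10,000 trials per setting) gives 0.106-0.112, 0.161-0.169 and 0.211-0.222 for prevalences of 5-40%.

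**Step 3. Ever/never per child, all weeks answered.** With no true effect, simulated rejection is 0.046-0.054, so the test holds its level.

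Power at p = 30%, ρ = 0.2, worked by formula:
- With s = (1 − ρ)/ρ = 4, P(no affected week in 6) = ∏ ((1 − p)s + k)/(s + k) for k = 0 to 5. Ever affected: 0.740 in control and, at p = 21%, 0.596 under treatment.
- Ever/never: difference 0.144, null SE √(2 × 0.668 × 0.332 / 96) = 0.0680, power about 0.56.
- Share of weeks: variance per child p(1 − p)(1 + 5ρ)/6 = 0.0700 and 0.0553; SE √(0.1253/96) = 0.0361; z = 0.09/0.0361 = 2.49; power Φ(2.49 − 1.96) = 0.70.

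The same formulas across settings:

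| p | ρ | ever/never | share of weeks |
|---|---|---|---|
| 30% | 0.1 | 0.60 | 0.82 |
| 30% | 0.2 | 0.56 | 0.70 |
| 30% | 0.3 | 0.53 | 0.61 |
| 10% | 0.1 | 0.32 | 0.32 |
| 10% | 0.3 | 0.24 | 0.21 |
| 5% | 0.1 | 0.19 | 0.18 |
| 5% | 0.3 | 0.15 | 0.13 |

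Simulation at 30% gives 0.52-0.60 against 0.59-0.82. At 5-10% there is no loss.

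**Step 4. Ever/never with unequal response and no true effect.** One arm answers all six weeks; every child in the other answers five or four. At p = 30%, ρ = 0.2, the ever-affected proportions are 0.740 (six weeks), 0.700 (five) and 0.647 (four) with the same underlying illness. Rejection rates over ρ = 0.1-0.3:

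| p | 5 v 6 weeks | 4 v 6 weeks |
|---|---|---|
| 30% | 8-12% | 20-42% |
| 10% | 7-9% | 12-26% |
| 5% | 6-7% | 9-17% |

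In simulation, a t-test on the share of reported weeks stays near 5%. These rows are an extreme case: a whole arm loses the same weeks and nothing is imputed.

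**Step 5. Kindergarten.** The share-of-weeks test is not valid by itself in a cluster trial. With an assumed 19 children per kindergarten and ICC 0.01-0.05, DE = 1 + 18 × ICC = 1.18-1.90, and actual α = 0.07-0.16. Any replacement needs a kindergarten term.

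**The case against.** The strongest reply is that the article commits neither error. It speaks only of frequencies, and the unit of a secondary tabulation may properly be left to an analysis plan that is not shown. Ever/never per child is a legitimate summary that holds its level under equal response, and preferring share of weeks is partly a choice of estimand. The power loss depends on prevalence and vanishes at 5-10%, which may be where gastrointestinal infection lies. The unequal-response figures assume a whole arm misses weeks and disregard the multiple imputation in section 2.8 and the reminders and calls in section 2.7. Weekly capture is explicit for cold and gastrointestinal symptoms, not for bronchitis, lung inflammation or antibiotic use. Nor are these the only illness-specific comparisons between arms, since CCQ scores are also compared.

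All of this stands as a limit on the point. A reader might infer that the plan will pool weeks, or that every use of the test gives a wrong answer; the article supports neither. Pooling and collapsing are not even the only options: a chi-square on the number of affected weeks per child is possible, though it would ignore the order of the counts and the weeks answered.

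What the reply does not remove is the stated choice of test. However the unit is defined, an unadjusted chi-square or Fisher test cannot take account of weeks answered or baseline, and the article itself uses a baseline-adjusted count model for the primary outcome. Imputation could reduce the response problem if applied to weekly records, but the article does not say that it will be. The arms are open-label, and the Discussion allows that caregivers may show response bias.

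**Conclusion.** The concern holds in a conditional form. For symptoms collected weekly, the named test is a poor match to the data.

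- If child-weeks are pooled as independent, false positives are about 11-22% at nominal 5%, for assumed ρ = 0.1-0.3.
- If weeks are collapsed to ever/never, the test is valid under equal response. At an assumed 30% weekly prevalence and ratio 0.7, its power is about 52-60% against 59-82%; at 5-10% there is no loss. The power argument therefore suits colds better than gastrointestinal infection.
- Ever/never is biased if the arms differ in weeks answered and imputation does not correct this. The article gives no sign of how large such a difference would be, so the Step 4 figures show direction and are not a forecast.

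The prevalences, correlation, ratio and kindergarten ICC are all assumptions. The change is worth making because the data are already planned for collection, but it concerns secondary outcomes only.

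**What to change.** For conditions captured on the weekly form (colds and gastrointestinal symptoms), replace the chi-square/Fisher test by a binomial or beta-binomial mixed model of weeks affected out of weeks reported per child in the 12-month window. Include group and the child's share of affected weeks in the baseline window as predictors, and a random effect for kindergarten, the randomised unit. Baseline adjustment should add precision if a child's tendency to illness persists over the year. State whether the multiple imputation covers the weekly records. Report rare conditions descriptively.

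The cost is analysis-plan wording and modest programming, with no extra data or children. The summary for these secondary outcomes changes from the risk of any episode to the share of weeks affected, which the sponsor should accept deliberately. The simulations checked a simple test on share of weeks, not this full model, so its behaviour with the actual number of kindergartens should be checked before it is fixed.

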**Figure 2 fig2:**
[figure not shown]
Curriculum overview. Kneipp Educator Training.

The waitlist group will also complete the training after the last data collection period. While there will be project mandate as to which interventions must be conducted, the educators in the intervention group will be encouraged to commence interventions directly after the training, particularly with emphasis and daily practice of cold-water applications. (see Figure 1: Five Elements of Kneipp) Intervention activities will be reported on a weekly basis by the kindergartens and recorded by the team. Furthermore, a qualitative methodology is employed to evaluate whether introducing the Kneipp concept will affect factors such as stress levels, quality of work in the kindergarten environment, interactions among children and educators. This involves conducting focused ethnography (15) on two separate days (one in spring/summer and one in autumn/winter) to obtain a better overview of the applications used in different seasons. Semi-structured interviews will be conducted with educators and kindergarten directors to understand and evaluate the use of the interventions, as well as to detect possible changes among kindergarten group dynamics and kindergarten educators. Maximum variation sampling strategy will be applied to provide rich and diverse perspectives, used for answering the qualitative research question. All kindergarten directors and at least 2 other educators from all the intervention facilities will be interviewed. The interviews will be conducted in the kindergarten facilities by a medical doctorate student (MG) until data saturation is reached. Throughout the process regular meetings with a group of qualitative researchers will be organized, where the means of data collection and analyzing process will be discussed, evaluated and reflected.

Another focus of the qualitative evaluation is to assess the feasibility of conducting larger multi-centric randomized studies in this context and the potential future implementation of hydrotherapy in kindergartens.

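### The set called ITT is defined by having kindergarten reports, not by allocation and baseline enrolment, and the ITT-versus-PP comparison does not test the missing-data assumption

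*Protocol article*

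**What the plan says.** All of the rules on analysis sets stand in section 2.8 (Statistical methods) of the protocol article.

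- Primary outcome: "The primary outcome will be the number of sick days reported to the kindergarten".
- Primary model: negative binomial regression. "This model will include the group (Kneipp vs. Control) and the number of sick days at baseline as predictors".
- ITT set: "The ITT population will include all children from whom kindergarten reports are available".
- Missing data: "For handling missing data in the ITT approach, multiple imputation will be used".
- PP set: "The PP population will consist of children who strictly followed the prescribed treatment and for whom complete data is available".
- Robustness: "Sensitivity analyses will also be performed to compare the results from the ITT and PP approaches to ensure robustness of the findings".

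Other sections bear on these rules. Sections 2.1 and 2.7 have kindergartens document absences in two 6-week periods, at baseline and 12 months later. Section 2.2 requires a child to be in care at a participating kindergarten during the study and gives no enrolment cut-off. Section 2.6 states that allocation is open to kindergartens, caregivers and children. Section 2.3 replaces a kindergarten that declines because of its allocation. Section 2.5 expects about 20% dropout and sets the target at 240 children.

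**The concern.** An intention-to-treat set is fixed by who was randomised, here through the kindergarten, and it does not depend on what data came back. The plan's set depends on exactly that, and the data in question carry the primary outcome. If leaving or joining differs between openly allocated arms, a set selected on reports no longer compares the groups that randomisation created.

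The definition also fits badly with the promise of multiple imputation, because some readings of it remove the very children whose outcomes would need imputing. Since no period is named, different analysis populations satisfy the same sentence, and the choice could be made after unblinded data have been seen. The trial is described as confirmatory, so its primary population should not be open in this way.

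**Working it through.** **Step 1. The plan's sample size.** Inputs from section 2.5: phi = 0.205, two-sided alpha 0.05, power 80%, dropout about 20%.

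- N = (1.960 + 0.842)² / 0.205² = 186.8, so 187. The noncentral chi-square calculation also gives 187.
- Allowing for dropout: 187 / (1 − 0.20) = 233.75, so 234. This is within 3% of the stated 240, and the figure is reproduced. No allowance for clustering enters it.

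**Step 2. How many children the definition affects.** At the planned dropout, 0.20 × 240 = 48 children have no 12-month report and 240 − 48 = 192 remain. Other loss rates are assumptions. Power is from the plan's own chi-square calculation, ignoring clustering.

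| Loss | Without 12-month report | Remaining | Power |
|---|---|---|---|
| 10% | 24 | 216 | 0.854 |
| 20% (plan) | 48 | 192 | 0.811 |
| 30% | 72 | 168 | 0.757 |
| 40% | 96 | 144 | 0.691 |

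At the planned loss, power is not the difficulty, since 192 exceeds 187. What matters is who the 48 are and whether they are analysed.

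**Step 3. Three readings of the ITT sentence.**

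| Report needed | Children who leave before 12 months | Children who join after allocation | Left for imputation in the primary model |
|---|---|---|---|
| (a) 12-month | Excluded (about 48) | Not barred | Missing baseline counts |
| (b) Both periods | Excluded (about 48) | Excluded | Almost nothing |
| (c) Either period | Kept if they have a baseline report | Not barred | About 48 outcomes, plus joiners' baseline counts |

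No reading ties membership to allocation or to enrolment at baseline.

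**Step 4. Kindergartens that decline after allocation.** Section 2.3 replaces them. A declining kindergarten that files no report contributes nobody to the set under (a), (b) or (c), while its replacement's children count as ITT. No stated rule is broken.

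**Step 5. The robustness comparison.** The PP set imposes two conditions at once, adherence and complete data. A difference between ITT and PP could come from either. Agreement between them shows nothing about children whose outcomes are missing, because the assumption behind the imputation is the same throughout. Under (a) and (b) both sets also condition on the 12-month outcome having been reported.

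**The case against.** The strongest counter-argument is that the text does not say the report must be the 12-month one. A child who leaves before the second period still has a baseline report. On an ordinary reading that child stays in, and imputation has a real task. The definition may even be meant generously, to keep a child whose parents did not respond. Imputation may also serve the weekly parent questionnaires and not only the primary count. This stands, and it limits what can be claimed.

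A reader might infer that the plan drops leavers, admits later joiners and empties the imputation all at once. The documents do not support that as fact. Dropping leavers while admitting joiners happens only under reading (a), and the period is not named. Late entry of children is not stated anywhere. The repeated onboarding questionnaire (section 2.7) is compatible with it, but section 4.2 describes later consent only for newly hired staff. The accurate statement is that late entry is not barred.

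A reader might also want to express the bias in sick days. The article gives no mean or spread of sick days and nothing on how leavers differ from stayers, so any such figure would rest on invented inputs.

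It can fairly be said that the plan calls the two sets a compliance analysis and never claims that comparing them tests missing data. Still, it is the only sensitivity analysis named, it directly follows the imputation sentence, and its stated purpose is robustness. Finally, the full imputation model and the PP adherence threshold are matters for an analysis plan, and their absence is not held against the article. The ITT definition is different, because the article states it.

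**Conclusion.** The point holds in this form: the set labelled ITT is an available-data set, its report period is not fixed, and it is anchored to neither allocation nor baseline enrolment. At the plan's own dropout rate, the choice of reading decides whether about 48 of 240 children (20%) are excluded or kept with imputed outcomes. Under readings (a) and (c), later joiners are not barred. Under all three, children of a declining kindergarten that files no report are lost.

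The PP comparison cannot serve as the check on missing data, because it changes adherence and completeness together and leaves the missing-data assumption untouched.

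The figure of 48 rests on the planned dropout and on taking dropout to mean no 12-month report. The direction and size of any bias cannot be derived from the article. The conclusion does not depend on them, because it follows from the definition.

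**What to change.** In section 2.8, or by amendment before data review:

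- Define ITT as all consented children enrolled at baseline in all randomised kindergartens, analysed by the arm to which their kindergarten was allocated.
- Exclude children who join after allocation from the primary set.
- Impute missing 12-month counts for children who leave, allowing for kindergarten and using the baseline count and parent-reported absences.
- Add a sensitivity analysis that varies the missing-data assumption.
- Keep ITT versus PP as a look at adherence if wanted, but do not present it as the check on missing data.

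The cost is a few sentences, slightly more analysis work and somewhat wider intervals. No new data are needed, and the target of 240 does not change.

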### Eligibility criteria

2.2

Eligibility crite shown in Table 1.

**Table 1 tab1:** Eligibility criteria.

	Inclusion criteria	Exclusion criteria
Kindergartens	Berlin kindergartens seeking certification as Kneipp daycare facilities with Kneipp-Bund e.V. Interested in participating in associated training via Sebastian Kneipp Academy. Willingness to engage in pair-randomized group assignment. Must provide pedagogical staff for training as Kneipp educators in autumn 2022 or 2023/24. Implementation of Kneipp concept immediately after training.	Kindergartens already implementing holistic health concepts (e.g., Kneipp, anthroposophical). Staff restricted from participating in training. Facilities unsuitable for implementing the Kneipp concept. Daycare center involved in another study preventing participation in this one.
Educators	Healthy educators, regardless of gender Working in the participating facilities 18–65 years of age Informed consent available	Serious chronic or acute illnesses inhibiting participation. Not speaking or understanding German
Caregivers	Caregivers, regardless of gender 18 years and older At least one child in a participating daycare center included in the study. Informed consent available	Serious chronic or acute illness preventing participation in the data collection. Not speaking or understanding German at the appropriate level for reading and completing study information
Children	Healthy children, regardless of gender 2–6 years Care in the participating kindergartens during study period Consent of the caregivers	Serious chronic or acute illness Not speaking or understanding German Age under 2y/o

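### A Shapiro–Wilk pre-test decides the scale of the CCQ comparison, and the one transformation named is undefined for a zero score

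*Protocol article*

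**What the plan says.** All of this is in the protocol article, Section 2.8 (Statistical methods), unless noted.

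- CCQ group comparison: "independent t-tests to compare the mean Common Cold Questionnaire (CCQ) scores between the Kneipp and Control groups".
- Subgroup analysis of the same score: "To investigate the interaction effects of group and sex, and group and age on CCQ scores, a two-way ANOVA will be performed".
- Assumption check: "normality of the data distribution for continuous outcomes will be assessed using the Shapiro–Wilk test".
- Consequence of the check: "If necessary, data will be transformed using appropriate methods, such as log transformation, to meet the assumptions on the statistical tests".
- Primary outcome (sick days): "we will employ a negative binomial regression model". The expected "right-skewed data because of high zero counts" refers to these counts, not to CCQ scores.
- Section 2.2 (Eligibility criteria) enrols "Healthy children, regardless of gender 2–6 years". Section 2.7 has caregivers report symptoms weekly for six weeks in each of two measurement periods.

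The article gives no offset for the log, no rule for zero scores, and no rank-based or zero-allowing alternative for the CCQ group comparison. It does not give the CCQ scoring range or say whether weekly or six-week scores are analysed. It also leaves open whether normality is checked on pooled data, by arm or on residuals.

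**The concern.** A significance test on the outcome data is a poor way to choose the analysis scale. At this sample size it detects skewness that hardly matters for a comparison of means. It therefore calls for a transformation because the sample is large, not because the t-test is failing.

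The transformation named makes this worse. Symptom scores in children enrolled as healthy may well include zeros, and the log of zero does not exist. The analyst must then remove those children, add a constant, or choose another transformation, after data collection and in a trial with open allocation. These choices test different things. A preventive measure could plausibly act by raising the share of symptom-free children, and that is where the choices diverge most. Any log scale also replaces the difference in mean CCQ score with a different quantity.

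**Working it through.** **Sample size in play.** Section 2.5 gives φ = 0.205, two-sided α = 0.05, power 80%, dropout about 20% and a total of 240 children.

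- N = (1.960 + 0.842)² / 0.205² = 7.849 / 0.04203 = 186.8, so 187.
- Allowing for dropout: 187 / (1 − 0.20) = 233.75, so 234. This is within 3% of the stated 240.
- Expected with data: 240 × 0.80 = 192, or 96 per arm if allocation is 1:1 (assumption).

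**How often the pre-test rejects.** Simulation, 2,000 runs per setting, Shapiro–Wilk at 5%. The article gives no CCQ distribution, so four assumed shapes were used for the non-zero scores, with 0–50% zeros added.

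| Non-zero part | n = 96 | n = 192 |
|---|---|---|
| Gamma, shape 2 (skewed) | 99.7–100% | 100% |
| Integer, negative binomial (skewed) | 99.95–100% | 100% |
| Gamma, shape 5 (mild skew) | 56–100% | 92–100% |
| Near-normal, no zeros | 4% | 4% |
| Near-normal, 2% / 5% / 10% zeros | 30% / 77% / 99% | 59% / 97% / 100% |

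Once zeros reach 20%, rejection is at least 99.5% for every shape at both sizes.

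**Whether the t-test needs rescuing.** With 96 per arm and gamma shape 2 scores, the untransformed t-test had a type I error of 5.0% at 20% zeros and 4.8% at 50% zeros (5,000 runs). Clustering was not simulated, so this speaks to skewness only. It does not show that an independent t-test is valid in this cluster trial.

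**Whether the log reaches its aim.** log(0) is −∞, and a t-test on such data returns no result. With log(x+1) and 5% or more zeros, Shapiro–Wilk still rejected in 96–100% of runs at n = 192. A spike at zero remains a spike after any one-to-one transformation, so the rule has no natural stopping point.

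**What the unstated choice does to power.** 96 per arm, 2,000 runs, benefit placed only in the symptom-free share, non-zero scores gamma shape 2 or integer, clustering ignored.

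| Zeros, control vs Kneipp | Raw t-test | Log, zeros dropped | log(x+1) | Mann–Whitney |
|---|---|---|---|---|
| 10% vs 25% | 30% | 5% | 58–59% | 44–45% |
| 20% vs 40% | 47% | 5% | 73–77% | 68–71% |
| 30% vs 50% | 50–51% | 5–6% | 72–73% | 71–72% |

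Dropping zeros would remove (10 + 25)/2 = 17.5%, (20 + 40)/2 = 30% and (30 + 50)/2 = 40% of children, unequally by arm. The remaining comparison is among ill children only, so power falls to α.

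**How common zeros might be.** This depends on the unit analysed. If weeks were independent (assumption), weekly zero shares of 50%, 70% and 90% leave 0.5⁶ = 1.6%, 0.7⁶ = 12% and 0.9⁶ = 53% of children with zero over all six weeks.

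**The case against.** A reader might infer that the plan throws symptom-free children out of the CCQ analysis and so loses the effect it seeks. The article does not support that. The log is offered as an example and only where a transformation is needed; exclusion of zeros appears nowhere. A method undefined on the data would hardly count as appropriate, and an offset is a common response. With log(x+1) every child stays in and power was higher than for the raw t-test in each setting tried. The 5% figure therefore describes one permitted route, not the plan.

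A reader might also infer that the pre-test is bound to reject. That depends on the shape of the score: near-normal scores without zeros gave 4%, and mild skew at n = 96 as little as 56%. Whether CCQ scores can be zero, and how often, is not in the article; over a six-week total, zeros could be rare. Nor does the article rank the CCQ above the other secondary outcomes. An analysis plan that is not shown may settle zeros, offset and score unit.

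These objections limit the size of the point but do not remove it. The article does more than leave detail open: it states a data-driven rule. That log(x+1) does well in some settings does not rescue the rule, because the same sentence permits analyses running from no power above α to the highest power of those compared. Skewness alone, without any zeros, still triggers the rule near n = 192 and still moves the analysis away from mean scores. It also stands that the raw-scale t-test is not the most powerful option, so the argument is for fixing the analysis in advance rather than for the raw scale as such.

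**Conclusion.** The point holds for a secondary outcome. Section 2.8 lets a normality pre-test on the trial data set the scale of the CCQ comparison, and it exposes the ANOVA on the same score. Near 192 children that test will almost always reject if scores are skewed or zero-heavy. The only transformation named is undefined at zero and departs from "compare the mean Common Cold Questionnaire (CCQ) scores between the Kneipp and Control groups".

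If symptom-free children occur and the benefit lies only in their share, the unstated handling of zeros moves power from about 5% to 30–51% or 58–77%. These figures rest on assumed zero shares, assumed score shapes, 96 per arm and no clustering. They show how much the choice could matter, not what will happen in this trial. The confirmatory primary analysis uses a negative binomial model and lies outside this rule.

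**What to change.** Delete the Shapiro–Wilk step and the conditional transformation for the CCQ. Replace the independent t-test with one CCQ analysis fixed before the groups are compared. It should:

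- state the score unit (weekly or six-week);
- keep all children, including those with a zero score;
- account for kindergarten clustering;
- adjust for baseline CCQ, which Section 2.4 already has collected;
- use robust or bootstrap standard errors suited to few clusters, or a model that allows zeros.

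Apply the same scale to the ANOVA with sex and age. Report any transformed or rank-based analysis as sensitivity only, with the offset stated if a log is used.

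Cost: a few lines of text and slightly more analysis work, with no new data. Standard errors will be wider if clustering is present.
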